#### Training of intervention providers

Intervention providers will deliver the intervention under the supervision of an expert team of physiotherapists (a senior lecturer, the first and fourth authors) [9, 21]. Each provider will receive two 2-h training workshops and 1 h of one-to-one supervision per participant to teach providers how to deliver the intervention and counsel participants in line with self-determination theory and motivational interviewing. The providers will be trained to spot any signs of barriers and lack of preparedness for exercise and for engaging in physical activity and will learn how to respond to distress or need for support in a manner that satisfies the need for autonomy, competence and relatedness. During the intervention period, the students and the expert team will attend regular evaluation meetings to ensure that the intervention providers feel prepared to deliver an individually tailored intervention.

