### Process evaluation research questions

The domains of the process evaluation will be examined by answering the following overarching research questions (further details are provided in Table 1):Is the intervention delivered with fidelity, and how do contextual characteristics structure fidelity?Is the intervention acceptable to the participants, the intervention providers and the healthcare managers, and how do contextual factors interact with acceptability?Does the intervention work in accordance with the proposed mechanisms of change, and how do contextual characteristics influence these mechanisms?

**Table 1 Tab1:** The process evaluation domains in relation to research questions, data sources and procedures

Domains	Research questions	Data sources	Procedures	When	Informants
**Implementation**	How do observations and experiences (context) relate to tailoring to each participant, and how do they relate to intervention fidelity?	Focus group interviews	Interview led by the last author (evaluation meetings)	Throughout trial	Intervention providers (*n* ≈ 10) and expert team^c^ (*n* ≈ 3)
		Online survey	Self-report: fidelity as the extent which intervention was delivered, 100 mm VAS	Six months	Intervention providers (*n* ≈ 10)
**Implementation**	Do baseline characteristics differ between participants who received high and low intervention doses and in participants and non-participants (intervention reach)?	Online record	Self-report	Baseline	Participants (*n* ≈ 100)
		Online record	Clinician registration: radiographical variables	Baseline	Participants (*n* ≈ 100)
		Online rating scale^b^	Self-report: exercise dose	Six months	Participants (*n* ≈ 100)
**Implementation** **(explorative)**	How does dose relate to changes in health outcomes?	Online PROM^a^	Self-report: pain, physical functioning and QOL	Baseline, 3 and 6 months	Participants (*n* ≈ 100)
		Online rating scale^b^	Self-report: exercise dose	Six months	Participants (*n* ≈ 100)
**Acceptability**	How do contextual factors relate to expectations and behavioural experiences?	1:1 semi-structured interviews	Interview led by the first author	Baseline and 6 months	Participants (*n* ≈ 15–20)
**Acceptability**	How prepared do providers feel to deliver the intervention?	Focus group interviews	Interview led by the last author (evaluation meetings)	Throughout trial	Intervention providers (*n* ≈ 10) and expert team^c^ (*n* ≈ 3)

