### Implementation

We will conduct a multi-component examination of the implementation of the intervention, including process, fidelity, dose and reach [21]. We will examine the implementation process by describing the required structures and resources, and we will measure fidelity as the degree to which the intervention is delivered as intended. Dose will be measured as the number of completed supervised and home-based exercise sessions. High dose is defined as completing a minimum of 75% of scheduled training sessions, medium as completing 50–74% and low as completing less than 50% [21]. Additionally, we will measure the dose using the exercise adherence rating scale (EARS) [29, 30]. Reach will be examined by describing baseline participant characteristics in those receiving a high compared versus a low dose, and by comparing the age and sex of participants with those of non-participants. In an additional explorative analysis, we will examine if the dose is associated with changes in health outcomes.

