#### Online fidelity survey

Intervention providers will use a 100-mm visual analogue scale (VAS) in a REDCap survey form to measure their ability to deliver specific content of the intervention, ranging from not possible (0) to always possible (100). The intervention components describe the ability to deliver the following: (1) use the Borg CR10 to determine the difficulty level and repetitions of exercises; (2) use the participant’s expressions of exercise acceptability to determine difficulty level and repetition; (3) use the intervention manual to determine correct exercise performance; (4) council participants about pain mechanisms in acetabular dysplasia, give advice on physical activity, monitor weight loss (if relevant) and deliver support to increase exercise adherence. The data will be used to examine intervention tailoring as an integral aspect of the implementation process.

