#### Semi-structured focus group interviews with the intervention providers and the expert team

Regular evaluation meetings designed as online focus group interviews with the intervention providers and the expert team will be conducted in the study period [9, 21]. A semi-structured interview guide has been developed and key questions are included in Table 3. Focus group interviews will focus on the quality of delivery, comprising challenges, tailoring and experiences with the MovetheHip intervention. Data from these interviews will be used to examine how the intervention providers tailor the intervention to the individual participant, considering their different exercise behaviours and physical and mental functioning as part of the implementation examination. In addition, data will reflect a consensus about tailoring for the individual participant and will show how well the intervention providers feel prepared to deliver the intervention.

**Table 3 Tab3:** Process evaluation domains, themes and key questions for interviews with intervention providers

Domain	Theme	Questions
*Participant behaviour*		
Concurrent acceptability	Exercises	Based on your observation of exercises, what challenges do the participants have when doing the exercises?
	Patient education	How do you experience that the participants comprehend your counselling about: - Acetabular dysplasia and pain mechanisms - Exercise and physical activity - Pain and overweight
Mechanisms of change	Motivation	How do you experience that the participants receive the incorporated flexibility of the intervention?
		How do you experience that the participants receive your feedback approach?
*Intervention provider behaviour*		
Concurrent acceptability	Exercises	What challenges do you have in instructing participants in the exercises?
	Patient education	What challenges do you experience when counselling about: - Acetabular dysplasia and pain mechanism? - Exercise and physical activity? - Pain and overweight?
Mechanisms of change	Motivation	How does it work for you to deliver the intervention with flexibility?
		How do you give feedback to the participants?
		How do you support or counsel the participants to integrate exercises and physical activity into everyday life?
		How do you approach counselling about acetabular dysplasia, pain, physical activity, etc.?
		What do you find is essential when you establish your relation to the participant?
*Participant tailoring*		

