Implementation	Exercises	Based on your observation of exercises, how do you experience the participants’ ability to adjust the exercises to their performance ability?
	Patient education	How do you experience the participants' ability to translate counselling into actions in everyday life?
*Intervention provider tailoring*		
Implementation	Exercises	How do you adapt the exercises to the individual participant?
		Which adaptations did you make to instruct the participants on how to perform the exercises?
	Patient education	When delivering the education component to the participants, what considerations did you have when adapting your guidance to the individual participant?
*Intervention provider experiences*		
Concurrent acceptability	Experiences	What are your overall experiences with the intervention regarding what works and opportunities for improvement?
		How do you perceive your quality of delivery?
		What do you think about the training you received?
		Do you feel sufficiently prepared to deliver the intervention?
		Was the training you received acceptable in terms of: - What worked? - Have you missed anything? - How you have used the expert team?

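### The provider fidelity scale rates ability to deliver rather than delivery, contrary to the protocol's own definition, and providers' views on training are sought with their supervisors present

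*Protocol article*

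**What the plan says.** The first overarching research question of the process evaluation is whether the intervention is delivered with fidelity. The Implementation section under Methods gives the definition: "we will measure fidelity as the degree to which the intervention is delivered as intended". Table 1 lists a provider survey against this domain, described as "Self-report: fidelity as the extent which intervention was delivered, 100 mm VAS", at six months, with about 10 intervention providers as informants.

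The section Online fidelity survey describes the same 100-mm scale differently. Providers use it to "measure their ability to deliver specific content of the intervention, ranging from not possible (0) to always possible (100". Four numbered components follow. The fourth joins counselling on pain mechanisms with the instruction to "give advice on physical activity, monitor weight loss (if relevant) and deliver support to increase exercise adherence". The section closes by assigning the results to a different purpose: "The data will be used to examine intervention tailoring as an integral aspect of the implementation process".

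On the provider interviews, the article states: "Regular evaluation meetings designed as online focus group interviews with the intervention providers and the expert team will be conducted in the study period". Table 1 gives these meetings as the only source on how prepared providers feel, and says the last author leads them. The section Training of intervention providers states: "Intervention providers will deliver the intervention under the supervision of an expert team of physiotherapists". The Table 3 guide for these meetings includes "What do you think about the training you received", and also asks whether providers feel sufficiently prepared and how they have used the expert team.

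**The concern.** There are two separate weaknesses in the provider data.

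The first is one of construct. Whether content could be delivered and whether it was delivered are different quantities. A provider may truthfully report that advice on physical activity was always possible while having given it only sometimes. If the RCT turns out neutral, readers will want to know whether the intervention was given and did not work, or was not given. High ability ratings would do little to separate these explanations, yet under the name of fidelity they could be read as evidence of delivery.

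The second is the setting. The providers are students, and the people who supervise them are in the meeting when they are asked to judge their training, their preparedness and their use of that same team. Answers in such a setting tend to be more favourable than those given privately.

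**Working it through.** No figure in the plan depends on this point, so there is none to reproduce. The check compares the passages and adds one simple relation.

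**1. Definition against instrument.** The Implementation section asks for the degree of delivery as intended, and Table 1 asks for the extent delivered. The Online fidelity survey section asks for ability, with anchors expressed as possibility. The first two agree with each other; the third does not agree with either. The third is the one that sets out what the provider is asked to rate.

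**2. What the ability scale can say about delivery.** For one component, consider the occasions on which it was indicated. Let *a* be the share on which delivery was possible and *d* the share on which it was given. Content that was given must have been possible, so *d* ≤ *a*. An accurate ability rating is 100*a*, the fidelity definition calls for 100*d*, and the overstatement is 100(*a* − *d*).
- With *a* = 1 and *d* = 1, it is 100(1 − 1) = 0 points.
- With *a* = 1 and *d* = 0, it is 100(1 − 0) = 100 points.

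The document gives neither *a* nor *d*, so the overstatement cannot be placed more narrowly than 0 to 100. If providers rate accurately, a low ability score does imply low delivery, but a high score leaves delivery open.

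**3. Stated use.** The survey section assigns the data to tailoring. Table 1 attaches the survey to a question covering both tailoring and fidelity. An ability rating may serve the first, but it does not measure the second as the article defines it.

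**4. Other evidence on delivery.**
- The time taken by supervised sessions is recorded.
- The weekly logbook counts completed supervised and home sessions, and the Exercise Adherence Rating Scale covers completion of the four exercises. The article uses both as measures of dose.
- Six-month interviews with about 15–20 participants ask about the individual instruction and feedback they received.
- Provider focus groups ask about quality of delivery, challenges and adaptations.

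These bear on delivery. None of them quantifies whether the education and counselling content was delivered as intended.

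**5. Who is in the room.** Table 1 lists about 10 providers and about 3 expert-team members as informants in the same meetings. Its footnote identifies the team as a senior lecturer and the first and fourth authors; the training section names the same people as the supervising team. The last author, who leads the meetings, is not listed in that team. No separate or confidential provider assessment of the training is described.

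**6. How much remained to be collected.** Trial status gives 76 of 200 participants enrolled in January 2024, with data collection planned to end by July 2026. Remaining: 200 − 76 = 124, and 124/200 = 62% across both arms. Most enrolment was then still ahead.

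**The case against.** The strongest reply is that the survey is meant to serve tailoring, as its own section says. Education follows individual needs, and exercise level follows preference, goals and resources. On a plain scale from never to always delivered, content rightly left out for a participant would count as poor fidelity. This stands, and it shapes the fix: the rating must be conditional on the content being indicated, with a not-relevant option throughout. It does not remove the conflict with the definition and with Table 1.

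On the meetings, the expert team are listed informants, and the meetings are intended to reach consensus on tailoring, so their presence has a purpose. The moderator is outside the team, and the guide invites criticism by asking what was missed and what could be improved. The article states that the team supervises; it does not say who runs the training workshops. All of this stands and limits the point to a risk of bias of unknown size.

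Three stronger readings are tempting and are not supported:
- A reader might infer that the data cannot show delivery or acceptability at all. The sources in step 4 of the working are real evidence on delivery, and answers open to bias are not uninformative.
- A reader might set about 10 ratings against about 100 × 8 = 800 supervised sessions. The article gives the number of providers, not the number of forms each completes. One form per participant at that participant's six-month point is not excluded.
- A reader might call component 4 uninterpretable because it joins four contents. The form is not shown, and the article does not say that each numbered component is a single line.

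**Conclusion.** The point holds in a limited form. As specified, the only quantitative provider measure of fidelity rates perceived ability, which contradicts the article's definition and the description in Table 1; content that was possible but not given could score 100. This is a conflict within the document, not a detail left to a fuller protocol. Any error would run towards overstating delivery, assuming providers rate accurately.

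In addition, providers' views on training, preparedness and use of the expert team are open to social-desirability bias, probably upward, because the supervising team attends. That direction is a judgement about the setting; the document offers no figure for it.

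Neither matter affects the RCT's outcomes or sample size. Both bear on how the process evaluation would be used to explain the trial result, and both should be corrected because the remedy is small.

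**What to change.** - Reconcile the Online fidelity survey section with the Implementation section and Table 1. Word each item and its anchors as how often the component was delivered when indicated for the participant, from *never* to *always*, with a *not relevant* option on every item.
- If component 4 is a single line, score its four contents separately.
- Keep the ability rating alongside, labelled as such, for the tailoring question.
- Ask the Table 3 block on training, preparedness and use of the expert team with only the last author and the providers present. Keep the tailoring discussion joint.

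The cost is an edit to a REDCap form, a slightly longer form for providers and a change to the meeting agenda. The main downside is that ratings already collected as ability cannot be pooled with the new ones and must be reported separately.

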#### Semi-structured interviews with participants

Participants will be invited to participate in semi-structured one-to-one interviews by purposeful sampling at baseline and at the 6-month follow-up. Sampling will take into account factors such as gender, age, employment status and reason for not undergoing surgery. Data saturation will be checked prospectively, and further data collection will be undertaken if needed. The mode of the interviews will be either physical or via a video connection according to the participant’s preference. Baseline interviews will focus on previous experiences and expectations to changes and behaviour (degree of external, integrated or internal motivation) and the influence of personal, interpersonal and organisational contextual factors. The 6-month follow-up interviews will focus on experiences with the intervention, its acceptability and the participant’s behaviour (degree of external, integrated or internal motivation), as well as the influence of personal, interpersonal or organisational contextual factors. A semi-structured interview guide is developed and key questions are included in Table 2. As mentioned above, the interview data will be used to examine the underlying mechanisms of change.

**Table 2 Tab2:** Process evaluation domains, themes and key questions for semi-structured one-to-one interviews with participants

Domains	Theme	Questions
***Baseline interview (pre-intervention delivery)***		
Prospective acceptability	Individual experiences	What are your experiences with exercising or being physically active?
	Expected contextual influences	What are your experiences about following a specific exercise programme?
	Individual expectations	What do you expect to gain from the participation?
Mechanisms of change	Individual expectations and beliefs about change, behaviour and motivation	What do you anticipate would inspire you to do exercises and physical activity?
	Expected contextual influences	What do you anticipate would stop you from exercising and doing physical activities?
***Six-month follow-up interview (post-intervention delivery)***		
Retrospective acceptability	Individual experiences	How would you describe your experience of being involved in the intervention?
		What did you enjoy most about the intervention?
		What did you find most challenging about the intervention?
		Which experiences do you keep from this intervention (sustainability)?
Mechanisms of change	Individual experiences	In what way has the intervention made a difference for you?
		You have received instructions from a personal instructor – What are your experiences with receiving individual instructions and getting feedback?
	Individual experiences and contextual influence	What encouraged you to get your exercises done?
		What prevented you from getting your exercises done?

#### Semi-structured focus group interviews with the intervention providers and the expert team

Regular evaluation meetings designed as online focus group interviews with the intervention providers and the expert team will be conducted in the study period [9, 21]. A semi-structured interview guide has been developed and key questions are included in Table 3. Focus group interviews will focus on the quality of delivery, comprising challenges, tailoring and experiences with the MovetheHip intervention. Data from these interviews will be used to examine how the intervention providers tailor the intervention to the individual participant, considering their different exercise behaviours and physical and mental functioning as part of the implementation examination. In addition, data will reflect a consensus about tailoring for the individual participant and will show how well the intervention providers feel prepared to deliver the intervention.

**Table 3 Tab3:** Process evaluation domains, themes and key questions for interviews with intervention providers

Domain	Theme	Questions
*Participant behaviour*		
Concurrent acceptability	Exercises	Based on your observation of exercises, what challenges do the participants have when doing the exercises?
	Patient education	How do you experience that the participants comprehend your counselling about: - Acetabular dysplasia and pain mechanisms - Exercise and physical activity - Pain and overweight
Mechanisms of change	Motivation	How do you experience that the participants receive the incorporated flexibility of the intervention?
		How do you experience that the participants receive your feedback approach?
*Intervention provider behaviour*		
Concurrent acceptability	Exercises	What challenges do you have in instructing participants in the exercises?
	Patient education	What challenges do you experience when counselling about: - Acetabular dysplasia and pain mechanism? - Exercise and physical activity? - Pain and overweight?
Mechanisms of change	Motivation	How does it work for you to deliver the intervention with flexibility?
		How do you give feedback to the participants?
		How do you support or counsel the participants to integrate exercises and physical activity into everyday life?
		How do you approach counselling about acetabular dysplasia, pain, physical activity, etc.?
		What do you find is essential when you establish your relation to the participant?
*Participant tailoring*		
Implementation	Exercises	Based on your observation of exercises, how do you experience the participants’ ability to adjust the exercises to their performance ability?
	Patient education	How do you experience the participants' ability to translate counselling into actions in everyday life?
*Intervention provider tailoring*		
Implementation	Exercises	How do you adapt the exercises to the individual participant?
		Which adaptations did you make to instruct the participants on how to perform the exercises?
	Patient education	When delivering the education component to the participants, what considerations did you have when adapting your guidance to the individual participant?
*Intervention provider experiences*		
Concurrent acceptability	Experiences	What are your overall experiences with the intervention regarding what works and opportunities for improvement?
		How do you perceive your quality of delivery?
		What do you think about the training you received?
		Do you feel sufficiently prepared to deliver the intervention?
		Was the training you received acceptable in terms of: - What worked? - Have you missed anything? - How you have used the expert team?

